**Calculation of sample size based on the primary outcome**

Due to the results of a randomized study which has compared a complex education intervention for the correct application of inhalers with a standard consultation, we presume a difference for the success of the intervention in the control- and intervention groups of 20%, with success rates of  $p_1=32\%$  and  $p_2=52\%$  [22]. To determine a significant difference between the control- and intervention group by the chi-square test (unrelated sample,  $\alpha = 0.05$ ;  $\beta = 0.8$ ), it is required, in due consideration of a drop-out rate of 15% after 6 months, a cluster size of 5 community pharmacies per group and a cluster effect (Intraclass Correlation Coefficient, ICC) of 0.02,  $n=122$  medication administrations of a dosage form e.g. eye drops or transdermal patches per group. With a cluster size of 10 community pharmacies per group the sample size of the dosage form increases to  $n=133$  per group. The calculation of the sample size is carried out on the level of dosage forms because then patients who apply for various dosage forms can be educated according to their individual drugs. The follow-up visit after 12 months will be described qualitatively.

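### The sample-size paragraph prints β = 0.8 (20% power), but 122 and 133 per group follow from a target power of 0.80 (β = 0.20): a minor labelling error that changes no sample size

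*Protocol*

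**What the plan says.** Protocol section 15, under the heading on sample size for the primary outcome, assumes success rates of 32% and 52%. It introduces the calculation with "To determine a significant difference between the control- and intervention group by the chi-square test (unrelated sample" and completes the bracket with α = 0.05 and β = 0.8. The other inputs are "a cluster effect (Intraclass Correlation Coefficient, ICC) of 0.02", a drop-out rate, and two scenarios for the pharmacies. The first scenario, stated together with the drop-out rate, reads "it is required, in due consideration of a drop-out rate of 15% after 6 months, a cluster size of 5 community pharmacies per group" and gives n = 122. The second, "With a cluster size of 10 community pharmacies per group", gives n = 133. The unit of n is given as "medication administrations of a dosage form e.g. eye drops or transdermal patches per group".

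No other part of the protocol states a power or a type II error. The significance threshold appears once more, under Statistical design in the same section, as p ≤ 0.05.

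**The concern.** β stands next to α in the bracket, in the position of an error rate, and the protocol does not define it otherwise. By the usual convention β = 0.8 is an 80% chance of missing the assumed difference, that is, 20% power. A trial sized on that basis would be far smaller than the one described, so the printed inputs and the printed sample sizes cannot both be right.

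Type II error is a design property on which an ethics committee or a later reader relies. The paragraph leaves two scenarios open, so the calculation may be repeated once the number of pharmacies is settled. Anyone repeating it from the printed inputs would start from the wrong value, and anyone weighing a null result would have the wrong miss rate in front of them.

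**Working it through.** **Inputs.** From the sample-size paragraph: p1 = 0.32, p2 = 0.52, α = 0.05, ICC = 0.02, drop-out 0.15, 5 or 10 pharmacies per group. Assumed: equal allocation (one n per group is printed), a two-sided test, no continuity correction.

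**Formula.** Chi-square test with pooled variance under the null hypothesis:

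n = [z(1−α/2)·√(2·p̄·(1−p̄)) + z(power)·√(p1(1−p1) + p2(1−p2))]² / (p2 − p1)²

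Here p̄ = 0.42, so √(2 × 0.42 × 0.58) = 0.6980, and √(0.2176 + 0.2496) = 0.6835. With z(1−α/2) = 1.960, the first term is 1.368. The result is rounded up, multiplied by 1 + (m − 1) × 0.02, rounded up, divided by 0.85 and rounded up again.

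**Step 1: the protocol's own figures, with power 0.80 (β = 0.20).** z(power) = 0.8416, so n = (1.368 + 0.575)² / 0.04 = 94.4, rounded up to 95.
- m = 5: 95 × 1.08 = 102.6 → 103; 103 / 0.85 = 121.2 → **122**.
- m = 10: 95 × 1.18 = 112.1 → 113; 113 / 0.85 = 132.9 → **133**.

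Both printed figures are matched exactly.

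**Step 2: β = 0.8 taken literally (power 0.20).** z(power) = −0.8416, so n = (1.368 − 0.575)² / 0.04 = 15.7, rounded up to 16.
- m = 5: 16 × 1.08 = 17.3 → 18; 18 / 0.85 = 21.2 → **22**.
- m = 10: 16 × 1.18 = 18.9 → 19; 19 / 0.85 = 22.4 → **23**.

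The printed 122 is about 5.5 times the first of these (122 / 22).

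**Step 3: alternatives tried.**

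| Setting | 5 pharmacies | 10 pharmacies |
|---|---|---|
| Printed | 122 | 133 |
| Power 0.80, two-sided | 122 | 133 |
| Power 0.80, two-sided, continuity correction | 135 | 146 |
| Power 0.80, one-sided | 96 | 105 |
| Power 0.90, two-sided | 162 | 176 |
| Power 0.20, two-sided | 22 | 23 |
| Power 0.20, two-sided, continuity correction | 32 | 36 |

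At power 0.80, applying drop-out before the design effect gives 121 and 133, and rounding only at the end gives 120 and 132. Rounding conventions therefore move the answer by at most 2 and cannot explain a gap of about 100.

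**Step 4: what may be said about achieved power.** The match in Step 1 needs the factors 1.08 = 1 + (5 − 1) × 0.02 and 1.18 = 1 + (10 − 1) × 0.02. The counts 5 and 10 were thus entered as administrations per cluster, although the text describes them as pharmacies per group. If they are the numbers of pharmacies, m is the number of analysed administrations per pharmacy. Effective n is analysed n divided by the design effect, and power = Φ[(0.20·√n_eff − 1.368) / 0.6835].
- 122 with 5 pharmacies: analysed 122 × 0.85 = 103.7; m = 103.7 / 5 = 20.74; design effect 1 + 19.74 × 0.02 = 1.3948; effective n = 74.3; power **69.9%**.
- 133 with 10 pharmacies: analysed 133 × 0.85 = 113.05; m = 11.305; design effect 1 + 10.305 × 0.02 = 1.2061; effective n = 93.7; power **79.7%**.

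With the protocol's own factors (1.08 and 1.18) the corresponding values are 80.7% and 80.6%.

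**The case against.** The strongest case against pressing this point is that it is a slip of notation with no effect on the design. The sample sizes stand in the same sentence and the next. Anyone who recalculated with β = 0.8 would get 22 or 23 and see at once that it was not meant. This stands, and it is why the point is minor. It does not make the printed value right, and no other place in the protocol corrects it.

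Three stronger readings are tempting, and the document supports none of them.
- **That the trial was planned at 20% power.** The printed n rules this out.
- **That the stated operating characteristics of the primary test are wrong in general.** α = 0.05 is stated in the same bracket, agrees with the p ≤ 0.05 threshold under Statistical design, and is not in error. Nor is it a fault that α is printed without its sidedness: the chi-square test comparing two groups is ordinarily non-directional, and only the two-sided value reproduces the printed n.
- **That replacing 0.8 by 0.2 makes the statement fully correct.** It reconciles inputs and n under the method used, but that method takes the number of pharmacies as the cluster size. Printing 80% as the achieved power beside 122 with 5 pharmacies would replace one wrong figure with another. This objection stands and shapes the fix.

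**Conclusion.** The protocol's only type II error figure is wrong as printed. β = 0.8 means 20% power, while 122 and 133 per group rest on a target power of 0.80 (β = 0.20) with two-sided α = 0.05. The difference is 60 percentage points on paper and nothing in enrolment, testing or conduct. It is a minor labelling error. The conclusion depends on the usual meaning of β and on the formula and step-by-step rounding shown, which match both printed figures exactly.

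The values of about 70% and about 80% for achieved power are a separate, conditional statement. They apply if 5 and 10 are numbers of pharmacies per group, and they assume ICC 0.02, 15% drop-out, equal numbers of administrations per pharmacy and a normal approximation.

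**What to change.** In the sample-size paragraph of section 15, replace β = 0.8 with: target power 1−β = 0.80 (β = 0.20). Present it as an input to the sizing. Adding that α is two-sided would be a courtesy to the reader, not a correction.

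Do not describe 80% as the power achieved by 122 with 5 pharmacies per group. State whether 5 and 10 are pharmacies per group or administrations per pharmacy. If they are pharmacies per group, restate the achieved power from a design effect based on administrations per pharmacy: about 70% for 122 with 5 pharmacies and about 80% for 133 with 10, with the assumptions listed.

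The relabelling costs one line and alters no sample size or procedure. The power restatement adds a sentence. Whether the sponsor then keeps the 5-pharmacy scenario at 122 is a separate design decision, which the relabelling does not settle.

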## **11. Study procedure**

The study will be carried out in community pharmacies with which other projects have already established cooperation. Prior to the start of the study, pharmacy staff will be informed of erroneous and correct administration of the different dosage forms (see inclusion criteria) known from the literature, the use of study materials, and the study procedure. After written informed consent of the head of the pharmacy and pharmacy staff, the pharmacies will be assigned to control or intervention group (cluster randomization). There will be exclusive control pharmacies and intervention pharmacies.

Pharmacy staff addresses potential study participants according to the inclusion criteria during daily routine in the community pharmacy. It is possible within the scope of this study to train the use of different dosage forms for the same patient or family caregiver. In order to identify a potential administration error, the pharmacy staff asks the patient or family caregiver to use the medicine (duration approx. 2-5 minutes). Such a demonstration is quite common in the context of the usual pharmaceutical counseling. The demonstration can be performed with the patient's drug itself or with a placebo. The pharmacy staff assesses a possibly incorrect administration by using a checklist defined in advance for a specific dosage form. Checklists and placebo materials are provided by the Department of Clinical Pharmacology and Pharmacoepidemiology. In the control group, pharmacy staff provides a standard consultation (duration approx. 3 minutes) followed by the provision of standardized information material, e.g. written step-by-step

instructions. In the intervention group, the staging algorithm (Fig. 1) is used to determine the individual level of the patient or caregiver according to the Transtheoretical Model. The stage "Maintenance", i.e. the permanent correct use of the drug, cannot be detected with this algorithm. The purpose of this model is to identify in particular those medicines users who are not aware of administration errors despite incorrect use of the drug and who may not be motivated to seek training or detailed counseling.

[figure not shown]

Figure 2. Staging Algorithm

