## **15. Statistical method**

### **Statistical design**

The error rate of the intervention group will be compared to the error rate of the control group by the chi-square test. The error rate of the medication administration before patient education will be compared to the error rate after the training by the McNemar test. A  $p\text{-value} \leq 0.05$  is considered as statistically significant. Feasibility of the education method into the daily routine of the community pharmacy and the contentment of the patients and family caregivers will be analyzed qualitatively. The influence of co-variables like dosage form, patient characteristics, educating person and number of drugs on the education success will be determined by logistic regression.

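### The sample sizes of 122 and 133 treat 5 and 10 as administrations per pharmacy, but the protocol calls them pharmacies per group; with 5 pharmacies per group, 122 gives about 70% power or less, not 80%

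*Protocol*

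**What the plan says.** The sample-size paragraph of protocol section 15 assumes success rates of 32% and 52%, a chi-square test at alpha 0.05, a value of 0.8 labelled beta, and "a drop-out rate of 15% after 6 months". Clustering enters as "a cluster size of 5 community pharmacies per group and a cluster effect (Intraclass Correlation Coefficient, ICC) of 0.02". The result is 122 "medication administrations of a dosage form e.g. eye drops or transdermal patches per group". The next sentence reads "With a cluster size of 10 community pharmacies per group the sample size of the dosage form increases to" 133 per group. Thus 5 and 10 are each called a cluster size and each described as a count of pharmacies in a group.

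Section 11 confirms that whole pharmacies are randomized. The statistical design part of section 15 states: "The error rate of the intervention group will be compared to the error rate of the control group by the chi-square test". No other part of the protocol fixes the number of pharmacies or the number of administrations expected from each.

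**The concern.** Cluster size (administrations per pharmacy) and number of clusters (pharmacies per group) pull the sample size in opposite directions. For a given total, more pharmacies mean fewer administrations in each, a smaller design effect and a smaller required total. The protocol has the total rise from 122 to 133 when 5 becomes 10. That fits a larger cluster size but not a larger number of pharmacies.

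The two readings are different trials. About 5 administrations from each of some two dozen pharmacies per group is one recruitment plan. More than 20 from each of 5 pharmacies is another, with a much larger design effect. At stake is whether the stated 80% power belongs to the design as worded.

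**Working it through.** **Inputs**, all from the sample-size paragraph of section 15: 32% v 52%, alpha 0.05, ICC 0.02, drop-out 15%. Three assumptions are added: alpha is two-sided (sidedness is not stated), 0.8 is the power, and pharmacies are of equal size.

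**1. Sample size without clustering.** Pooled-variance formula, mean proportion 0.42, no continuity correction:

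n = [1.96·√(2·0.42·0.58) + 0.8416·√(0.32·0.68 + 0.52·0.48)]² / 0.20² = (1.368 + 0.575)² / 0.04 = 94.4, so 95 per group.

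**2. Reproducing the protocol's figures.** Design effect 1 + (m − 1)·0.02, where m is administrations per pharmacy. Round up, divide by 0.85, round up.

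| m | Design effect | Evaluable | Enrolled |
|---|---|---|---|
| 5 | 1.08 | 95·1.08 = 102.6 → 103 | 103/0.85 = 121.2 → 122 |
| 10 | 1.18 | 95·1.18 = 112.1 → 113 | 113/0.85 = 132.9 → 133 |

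Both match exactly. The variants tried do not give the pair: continuity correction gives 135 and 146, unpooled variance 118 and 129, and drop-out applied as a factor of 1.15 about 118 and 129.

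**3. Pharmacies implied by that calculation.** On enrolled counts, 122/5 ≈ 24 and 133/10 ≈ 13 per group. On evaluable counts, 103/5 ≈ 21 and 113/10 ≈ 11 to 12.

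**4. Power if 5 and 10 are pharmacies per group, one dosage form.** With k pharmacies, m = evaluable/k.

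| | 122 enrolled, k = 5 | 133 enrolled, k = 10 |
|---|---|---|
| Evaluable (×0.85) | 103.7 | 113.05 |
| Per pharmacy | 20.7 | 11.3 |
| Design effect | 1.395 | 1.206 |
| Effective n | 74.3 | 93.7 |
| Power, normal approximation | 69.9% | 79.7% |
| Power, cluster-level t-test, 2k − 2 df | 60.1% (8 df) | 76.4% (18 df) |

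For k = 5 the normal figure is Φ[(0.20·√74.3 − 1.368)/0.6835] = Φ(0.52). The t figure uses noncentrality 0.20/√(0.4672/74.3) = 2.52 against a critical value of 2.306. A beta-binomial simulation of the cluster-level t-test (40,000 trials) gave 60% for 5 pharmacies and 75% for 10.

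**5. Size needed for 80% on that reading.** With n₀ = 95, evaluable n = n₀(1 − ρ)/(1 − n₀ρ/k):

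- k = 5: 93.1/0.62 = 150.2, or about 177 enrolled.
- k = 10: 93.1/0.81 = 114.9, or about 135 enrolled.

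These are normal-approximation figures. By the t-test, 177 gives about 71% and 135 about 77%; 80% needs about 265 and 149. On either basis the required number falls as pharmacies are added.

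**The case against.** **It may be only a label.** The arithmetic is correct for clusters of 5 and 10 administrations. If that was meant, 80% power stands and only the description is wrong. This stands, and it makes the power loss conditional. It does not remove the error, because the paragraph says pharmacies twice and the two readings need very different numbers of them.

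**The planned chi-square test would still reject about 80% of the time.** Simulation of 122 enrolled in 5 pharmacies gave 80.2%. However, the unadjusted test then has a type I error of about 9.7%, so this is not 80% power at alpha 0.05. The 60% figure does depend on a cluster-level t-test that the protocol does not name. The choice of clustered analysis may sit in a statistical analysis plan that is not at hand, which is why both figures are given.

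**The sizes are per dosage form.** If several forms were pooled for the primary comparison, the number per group would exceed 122. As an illustration, three forms at 122 each in 5 pharmacies (366 enrolled, 311 evaluable, design effect 2.22), with the same ICC and administrations otherwise independent, give about 93% (normal) or 86% (t). The 70% and 60% therefore apply to an analysis of one form, which is the level at which the protocol sets its size.

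**Drop-out could be lower.** With all 122 evaluable, power in 5 pharmacies is 74.7% (normal) or 64.8% (t), still short of 80%.

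A reader might also infer that the reversed direction steers the sponsor to the weaker design. The protocol does not show a choice of 5 pharmacies over 10, so that is not claimed.

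**Conclusion.** The paragraph is wrong as written. The figures 122 and 133 belong to 5 and 10 administrations per pharmacy. The text attaches them to 5 and 10 pharmacies per group and has the required number move the wrong way.

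The consequence is conditional. For one dosage form in 5 pharmacies per group, power is about 70% (normal) or 60% (t, 8 df), a shortfall of roughly 10 to 20 percentage points. For 133 in 10 pharmacies it is about 80% or 76%, so that option is nearly unaffected. A reader might conclude that the trial is underpowered outright, or in both options. The document does not support that, since it leaves open which reading was intended.

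The results rest on the protocol's own rates, ICC and drop-out, two-sided alpha and equal pharmacy sizes; unequal sizes would lower power further. The value labelled beta can only be the power, because the figures reproduce at 80%. That is a minor labelling slip.

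**What to change.** Correct the paragraph in one of two ways.

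- **(a)** Describe 5 and 10 as administrations per pharmacy, keep 122 and 133, and state the implied pharmacies per group with the basis: about 24 and 13 on enrolled counts, or about 21 and 11 to 12 on evaluable counts.
- **(b)** Keep 5 and 10 as pharmacies per group and restate the power for one dosage form: 122 in 5 gives about 70% (normal) or 60% (t), and 133 in 10 gives about 80% or 76%. If a required size is quoted instead, name its basis: about 177 and 135 by the normal approximation, about 265 and 149 by the t-test.

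In either case remove the statement that the number increases with more pharmacies, and write power = 0.8 (beta = 0.2).

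The rewording costs one paragraph and no patients. Under (a), the stated sizes need more pharmacies than the text now names. Under (b), restating the power costs only a less favourable figure, whereas restoring 80% in 5 pharmacies would take 177 − 122 = 55 (normal) to 265 − 122 = 143 (t) more administrations per group.

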## **1. Summary**

Correct prescription, dispensing and administration of drugs are crucial for safe pharmacotherapy. In hospitals, almost every fifth drug dose is administered erroneously. It is supposed that at home, where patients or family caregivers are responsible for correct drug administration, error rates are even higher. Patient education on correct medication administration increases adherence and safety of administration. When comparing different educational interventions, it became evident that they differ significantly in their effectiveness. Training that addresses the individual needs of the patient is more effective than interventions that provide general information. A previous focus group study with patients, family caregivers, and nurses (ethics vote S-206/2013), which aimed at determining drug administration problems, revealed that many medicine users were unaware of drug administration errors. To address the lack of error awareness, the Transtheoretical Model developed by James D. Prochaska and his colleagues provides a theoretical framework. This model involves five different levels that a person goes through when he intrinsically changes his behavior. Studies to improve compliance show that level-specific measures, according to the Transtheoretical Model, positively influence the outcome of an intervention. Therefore, this prospective randomized controlled study, aims to evaluate standardized patient education in community pharmacies. This study takes into account the possibly lacking error awareness of the patient or family caregiver and feasibility in community pharmacies. Pharmacy staff will be trained on the study procedure, use of study material and correct administration of different dosage forms. Subsequently, pharmacy staff includes patients during their daily routine into the study. In a before and after comparison of the intervention group with the control group and follow-up visits, the effectiveness and sustainability of patient education will be evaluated

[figure not shown]

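### The sample sizes of 122 and 133 per group assume equal-sized pharmacies and enter the number of pharmacies as the number of administrations per pharmacy, so the stated 80% power does not hold for 5 pharmacies per group and is lowered further by unequal recruitment

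*Protocol*

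**What the plan says.** The trial randomizes whole pharmacies (protocol, sections 6, 10 and 11). Section 15, on sample size, assumes success rates of 32% and 52%, alpha 0.05, a value of 0.8 that is printed as beta and can only be meant as power, "in due consideration of a drop-out rate of 15% after 6 months", and "a cluster size of 5 community pharmacies per group and a cluster effect (Intraclass Correlation Coefficient, ICC) of 0.02". The result is 122 administrations of one dosage form per group. It continues: "With a cluster size of 10 community pharmacies per group the sample size of the dosage form increases to" 133.

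On recruitment, section 1 says "Subsequently, pharmacy staff includes patients during their daily routine into the study", and section 11 says "Pharmacy staff addresses potential study participants according to the inclusion criteria during daily routine in the community pharmacy". The protocol gives no minimum, target or maximum per pharmacy.

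On analysis, section 15 says "The error rate of the intervention group will be compared to the error rate of the control group by the chi-square test". It states no adjustment for pharmacy in that comparison.

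**The concern.** A cluster design effect depends on how many observations each cluster supplies and on how unevenly they are spread. If the formula assumes equal pharmacies while recruitment follows daily routine, the information in a fixed total is smaller than planned. With only 5 or 10 pharmacies per group, uneven recruitment can matter: one pharmacy of five supplying half of a group, with the rest equal, already gives a CV of 0.75.

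The same sentence raises a second question that cannot be kept apart from the first. The effect of unequal sizes scales with the mean number per pharmacy, and the protocol's inputs do not show what that number is. The required total also rises when the pharmacies per group double from 5 to 10. With the ICC fixed, more pharmacies should lower it.

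At stake is whether the primary comparison has its stated power, or, if clustering is ignored in the test, its stated 5% error rate.

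**Working it through.** **Inputs from the protocol, section 15:** success 32% versus 52%; alpha 0.05, taken as two-sided because that reproduces the figures; power 80%; drop-out 15%; ICC 0.02; 5 or 10 pharmacies per group. **Assumed:** the CV of pharmacy size, which the documents do not give; 0 to 1.0 is shown.

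**1. Reproducing the stated figures.** Mean success is 0.42. Without clustering, n per group = [1.960 × √(2 × 0.42 × 0.58) + 0.842 × √(0.32 × 0.68 + 0.52 × 0.48)]² / 0.20² = 94.4, so 95.

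Equal-size design effect: 1 + (m − 1) × 0.02.
- m = 5: 95 × 1.08 = 102.6, so 103; 103 / 0.85 = 121.2, so **122**.
- m = 10: 95 × 1.18 = 112.1, so 113; 113 / 0.85 = 132.9, so **133**.

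Both match exactly. There is therefore no hidden allowance for unequal sizes, and the number of pharmacies per group sits in the place of m, the number of administrations per pharmacy.

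**2. The mean size that the stated totals imply.**
- 122 × 0.85 = 103.7 analysed; 103.7 / 5 = 20.7 per pharmacy.
- 133 × 0.85 = 113.05 analysed; 113.05 / 10 = 11.3 per pharmacy.

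With 10 pharmacies, the m used (10) happens to be close to the implied 11.3. With 5, the m used (5) is about a quarter of the implied 20.7.

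**3. Design effect with unequal sizes:** DE = 1 + ((1 + CV²) × m − 1) × ICC. Power comes from the two-proportion normal approximation with analysed n / DE per group. It describes an analysis that allows for clustering.

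| Pharmacies per group | CV (assumed) | DE | Effective n | Power |
|---|---|---|---|---|
| 5 (122 enrolled) | 0 | 1.395 | 74.3 | 69.9% |
| | 0.4 | 1.461 | 71.0 | 67.9% |
| | 0.65 | 1.570 | 66.0 | 64.7% |
| | 1.0 | 1.810 | 57.3 | 58.5% |
| 10 (133 enrolled) | 0 | 1.206 | 93.7 | 79.7% |
| | 0.4 | 1.242 | 91.0 | 78.5% |
| | 0.65 | 1.302 | 86.9 | 76.6% |
| | 1.0 | 1.432 | 78.9 | 72.5% |

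Example for 5 pharmacies and CV 0.4: 1 + (1.16 × 20.74 − 1) × 0.02 = 1.461; 103.7 / 1.461 = 71.0.

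**4. Splitting the loss.** With 5 pharmacies, about 10 points (80% to 70%) are lost at equal sizes, through the entry for m. Imbalance costs a further 2 points at CV 0.4 and about 11 at CV 1.0. With 10 pharmacies, nearly all of the loss is imbalance: about 1 point at CV 0.4 and 7 at CV 1.0.

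**5. Under the unadjusted chi-square test.** The test statistic's variance is inflated by DE, so the two-sided type I error is 2 × [1 − Φ(1.96 / √DE)].
- 5 pharmacies: √1.395 = 1.181, 1.96 / 1.181 = 1.66, giving 9.7% at equal sizes; 10.5% at CV 0.4; 14.5% at CV 1.0.
- 10 pharmacies: 7.4%, 7.9% and 10.1%.

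The apparent power of that test with 5 pharmacies stays at 79.6% (equal) to 76.6% (CV 1.0), but at the inflated error rate.

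**The case against.** The strongest objection is that unequal size is a minor matter here. If 5 really were the number of administrations per pharmacy, a CV of 1.0 would move power only from 80.7% to 77.1%, and moderate imbalance costs 1 to 2 points in every scenario. This stands as far as imbalance alone goes. It does not rescue the plan, because 122 administrations in 5 pharmacies cannot average 5 each.

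A reader might infer that uneven recruitment is why power falls short. The figures do not support that for 5 pharmacies: most of the shortfall is there with equal sizes unless the CV is near 1.0.

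A reader might also infer that one busy pharmacy will dominate a group and that its staff's scoring will drive the result. The protocol does not show this. It says only that recruitment happens in daily routine and gives no data on pharmacy volume. Scoring uses a checklist defined in advance, and staff of the coordinating department may carry out follow-up assessments.

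The power figures presuppose a cluster-adjusted analysis, which the protocol does not name. That is fair, and it is why the type I error is shown as well. A separate statistical analysis plan may add such an adjustment; it is not at hand.

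Finally, a recruitment number per pharmacy is largely operational, and the protocol foresees a pilot phase in which procedures can be adjusted. A hard cap would not settle the matter in any case. With a cap of 1.5 times the average, five pharmacies at 1.5, 1.5, 1.5, 0.25 and 0.25 times the average comply and still give a CV of 0.61.

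**Conclusion.** The point holds in limited form. The sample-size calculation has no term for unequal pharmacy size, nothing in the recruitment procedure makes sizes equal, and the number of pharmacies was entered as the number of administrations per pharmacy. For 5 pharmacies per group, the stated 80% is about 70% at equal sizes and lower with imbalance. For 10, it is about 80% at equal sizes and falls modestly unless sizes vary strongly. If the chi-square test is used without adjustment, the consequence is mainly a type I error of roughly 10% to 14.5% (5 pharmacies) or 7% to 10% (10 pharmacies) in place of 5%.

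These results rest on the protocol's ICC and success rates, on assumed CVs, and on a normal approximation. With 5 pharmacies per group, a t reference with 8 degrees of freedom lowers power further, to about 60% at equal sizes. The part due to imbalance is minor and its size is uncertain. The part due to the entry for m does not depend on any assumed CV.

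**What to change.** In the sample-size paragraph of section 15:

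1. State the number of pharmacies per group and the expected analysed administrations per pharmacy (m) as separate inputs.
2. Use the design effect 1 + ((1 + CV²) × m − 1) × ICC with a stated CV range, such as 0 to 1.0 with a planning value of 0.4.
3. Restate the power for 122 in 5 pharmacies and 133 in 10.
4. In the statistical design paragraph, analyse the primary outcome with a method that allows for pharmacy, in place of the plain chi-square test.

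A planned recruitment number per pharmacy may be added as an operational aim. A hard cap is optional and does not by itself secure the assumed CV.

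The cost of restating is a text change. Restoring 80% power costs more. With m = 95 × 0.98 / (k − 95 × 0.02 × (1 + CV²)) for k pharmacies per group, k × m is the number analysed. Five pharmacies then need 151 analysed, 178 enrolled per group, at equal sizes, and 167 analysed, 197 enrolled, at CV 0.4. Ten pharmacies need 136 and 142 enrolled. Using 10 pharmacies per group is therefore the cheaper route in administrations, at the price of running more sites.
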